### DFC Characteristics Computation

#### Group Independent Component Analysis

After preprocessing, the resting state data of all participants will be analyzed using spatial independent component analysis implemented in GIFT^2^ to decompose the data into functional networks that exhibit a unique time course profile.

Reduction steps will be carried out at the subject- and group-levels. Subject-specific data will be reduced to 120 components, then concatenated across time. Next, at the group level, data will be reduced to 100 independent components using the expectation-maximization algorithm. Reliability and stability of the infomax independent component analysis algorithm in ICASSO will be ensured by repeating the algorithm 20 times.

The resulting components will be clustered to estimate their reliability and components with values >0.80 will be saved. Subject-specific spatial maps and time courses will be obtained using the back-reconstruction approach.

#### Dynamic functional connectivity

##### Sliding Window Approach

Sliding window analysis will be applied using the DFC network toolbox in GIFT. Resting state data will be separated into windows of 22 repetition times (44 s), and the regularized inverse covariance matrix will be used as covariance estimation using shorter time series can be noisy. An additional L1 norm of the precision matrix will be imposed to promote sparsity in the graphic LASSO framework with 100 repetitions. Subsequently, the functional connectivity matrices will be transformed to z-scores using Fisher’s z-transformation and covariates (age, gender, and education) will be regressed out.

##### Clustering analysis

A K-means clustering algorithm will be applied to the windowed functional connectivity matrices to assess the recurring functional connectivity patterns (states), as expressed by the frequency and structure of these states. Then a cluster validity analysis will be performed on the exemplars of all subjects to estimate the optimal number of clusters. We will use a subset of windows (local maxima in functional connectivity variance) as subject exemplars to decrease the redundancy between windows and computational demands. The reproducibility of functional connectivity states will be established using bootstrap resampling and split-half sample methods. The optimal number of clusters will be set to *k* = 2 following previous studies which is determined based on the silhouette criterion of cluster validity index (Rousseeuw, 1987; Fiorenzato et al., 2019).

### Outcome Measures

All measurements will be conducted before the intervention begins (baseline), immediately after the 24 weeks of intervention, and 12 weeks after the intervention.

#### Participants’ Characteristics

Demographic characteristics of all participants will be assessed prior to intervention including age, gender, education, age of onset, disease duration, body mass (kg/m^2^), height (cm), and family situation (see Table 1). Levodopa equivalent daily dosages will be calculated for PD patients (Tomlinson et al., 2010).

**TABLE 1 T1:** Demographic characteristics.

	Wuqinxi (*n*)	Balance (*n*)	HC (*n*)	Whole PD vs. HC (*t*/*x*^2^, *p*)	Wuqinxi vs. Balance (*t*/*x*^2^/*F*, *p*)*
Age (year)					
Gender (male%: female%)					
Education (year)					
Age of onset (year)				–	
Hoehn and Yahr stage, *n* (%)					
1–1.5				–	
2–2.5				–	
3				–	
Disease duration				–	
Body mass (Kg/m^2^)					
Height (cm)					
Family situation					
Living along					
Living with husband/wife					
Living with husband/wife and children					
LEDD				–	*****

*The Chi-square test will be used for categorical variables, and two-sample t-test will be run to test between group differences for continuous variables. LEDD = levodopa equivalent daily dose. *Two-factor repeated ANOVA will be applied.*

#### Primary Outcome Assessment

The Montreal Cognitive Assessment (Nasreddine et al., 2005) will be conducted to assess cognitive impairment and the Repeatable Battery for the Assessment of Neuropsychological Status (Stella et al., 2013) will be used to measure the cognitive domains of immediate memory, visuospatial, language, attention, and delayed memory (see Supplementary Table 1). Dynamic states, dwell times, fractional windows, and number of transitions will be computed to reflect the characteristics of DFC (see Supplementary Table 1).

#### Secondary Outcome Assessments

The Parkinson’s Disease Sleep Scale (PDSS) will be used to measure the severity of sleep disturbances (Trenkwalder et al., 2011); Parkinson Disease Questionnaire (PDQ-39) will be used to assess PD-specific health quality over the previous month (Jenkinson et al., 1997); Timed Up and Go Test (TUGT) will be used to evaluate mobility and motor ability (Zampieri et al., 2010); Unified Parkinson’s Disease Rating Scale Part III (UPDRS-III) will be used to measure motor symptoms (Haaxma et al., 2008); Hamilton Depression Scale [HAMD] (Bech et al., 1981) and Hamilton Anxiety Scale[HAMA] (Shear et al., 2010) will be used to evaluate depression and anxiety in both PD patients and HC (see Supplementary Table 1).

### Statistical Analysis

Following a previous study (Fiorenzato et al., 2019), we will investigate the temporal properties of DFC states by computing the average dwell time and fractional windows in each state, as well as the number of transitions from one state to another.

#### Replication of the previous effects

##### Clinical and Neuropsychological Data Analysis

Statistical analyses will be performed using SPSS version 19.0. Demographic and clinical information of all PD patients will be compared using two-sample independent *t*-test (see Table 1). Pearson’s chi-square test will be used to compare categorical variables (see Table 1). Pearson’s correlation analyses will be applied between temporal properties and cognition (MoCA and cognitive performance in each domain) in whole PD patients as well as motor severity (UPDRS-III) before the intervention (see Table 2). The threshold for statistical significance will be set at *p* < 0.05.

**TABLE 2 T2:** Correlation between dynamic functional connectivity temporal properties and clinical characteristics (before intervention, after intervention, and follow-up).

		UPDRS-III	MoCA	Cognitive domains				
				I-M	V	L	A	D-M
Dwell time state I	*r*							
	*p*-Value							
Dwell time state II	*r*							
	*p*-Value							
Fractional windows	*r*							
	*p*-Value							
Number of transitions	*r*							
	*p*-Value							

*I-M = immediate memory; V = visuospatial; L = language; A = attention; D-M = delayed memory.*

##### Group differences in dynamic connectivity: temporal and properties and strength

Group (whole PD patients vs. HC) differences in dwell time, fractional windows, and number of transitions will be examined using two-sample independent *t*-test analysis (*p* < 0.05, FDR correction, see Supplementary Table 1). Covariates will include education, levodopa and dopamine agonist equivalent daily doses. Subsequently, subject-specific medians corresponding to each group-level state will be estimated and two-sample independent *t*-test analysis will be used to compare the connectivity strength of each state at each unique regional pairing (*p* < 0.05, FDR correction) between groups (whole PD patients vs. HC), see Supplementary Table 1. Further, two-sample independent *t*-test analysis will be performed to compare strength abnormalities associated with cognitive deficits by comparing whole PD patients and HC (*p* < 0.05, FDR correction), see Supplementary Table 1.

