**FIGURE 1 F1:**
[figure not shown]
Study pipeline.

A recently published protocol “Long-Term Wu Qin Xi Exercise on Response Inhibition and Cortical Connectivity in Parkinson’s Disease: Design and Implementation of a Randomized Controlled Clinical Trial” is similar to the current protocol (Wang Z. et al., 2021). Our protocol considers the whole brain and will use resting-state fMRI to detect the effects of Wuqinxi on PD patients, while the previously published one only take the primary motor cortex and response inhibition related brain regions (dorsal lateral prefrontal cortex, right inferior frontal gyrus, and presupplementary motor area) into consideration and use dual-site paired-pulse transcranial magnetic stimulation to evaluate the cortical connectivity.

We will first follow the methods in Fiorenzato and Kim’s researches to replicate the effects in their work (Kim et al., 2017; Fiorenzato et al., 2019), and then use DFC analysis as the main method to detect the effects of wuqinxin intervention in patients. In order to replicate the effects in Fiorenzato and Kim’s study, HC will be recruited and compared with whole PD patients before the intervention to support that DFC method could be used in our participants. HC will not be involved in the intervention procedure.

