### Sample Size Calculation and Blinding

Sample size estimation was performed by G^∗^power V3.1 software (Franz Faul, Universitat Kiel, Germany). According to the analysis, at least 44 participants should be recruited (22 participants per group) in order to be able to perform two-factor repeated ANOVA (within-between interaction) with a middle effect size of 0.25 (Cohen, 1988), level of significance of 0.05, and power of 95% (Mayr et al., 2007). Since some participants may need to be dropped from the analysis due to excessive head motion during scanning, 40 participants will be recruited for each PD subgroup and 40 HC will be recruited. According to a similar studies published recently (Fiorenzato et al., 2019; Chen et al., 2021), this sample size should be adequate for replicating the previous effects in Fiorenzato’s study. In order to attract more participants, we will offer generous compensation and long-term health guidance. Every participant will be offered with an individual exercise plan when the whole study was completed. Randomization of PD patients will be done at the website www.random.org. Two researchers will be trained to assess the outcomes, and they will be blinded to group and will not participate in any interventions.

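### The baseline PD-versus-HC comparison is written as a two-sample t-test with covariates; no model that could carry them is named, and the variance assumption is left open at 80 versus 40

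*Protocol article*

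**What the plan says.** The protocol article plans a baseline check that dynamic functional connectivity (DFC) behaves in these participants as in earlier work: "HC will be recruited and compared with whole PD patients before the intervention". Under Replication of the previous effects, in the subsection on group differences in dynamic connectivity, the test is fixed as follows: "Group (whole PD patients vs. HC) differences in dwell time, fractional windows, and number of transitions will be examined using two-sample independent" t-test analysis, with FDR correction. The sentence after it adds: "Covariates will include education, levodopa and dopamine agonist equivalent daily doses". The same subsection then uses two-sample t-tests, with no covariates named, for connectivity strength at each regional pairing. The footnote to Table 1 also names the two-sample t-test for continuous variables.

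Three other places bear on the point:

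- Group sizes, under Sample Size Calculation and Blinding: "40 participants will be recruited for each PD subgroup and 40 HC will be recruited".
- An earlier adjustment of the windowed connectivity matrices, under Sliding Window Approach: "covariates (age, gender, and education) will be regressed out". Dose is not in that list.
- Participants' Characteristics, where levodopa equivalent dose is calculated for PD patients, and Table 1, where the PD-versus-HC cell for it is a dash.

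The article does not say whether the t-test is the equal-variance or the Welch form, and it gives no SDs for any DFC measure.

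**The concern.** The test and the covariate sentence do not fit together. In the matching subsection on the Wuqinxi and balance groups the same covariates are attached to a repeated-measures ANOVA, which can be extended to hold them. Here they are attached to a test that cannot. An analyst has to pick a way round this: drop the covariates, residualise first and t-test the residuals, or move to a regression model. These choices can give different answers.

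The second issue is conditional. Pooling both PD arms against one control group gives a 2:1 size ratio. At that ratio the equal-variance t-test loses its error control if patients and controls differ in spread, and patients and controls may well do so.

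At stake is the contrast that is meant to show that DFC can be used in this population. DFC measures are among the primary outcomes. The same t-test is also repeated over every regional pairing, and FDR correction does not repair p-values that are miscalibrated to begin with.

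**Working it through.** **The plan's own figure.** The article states "at least 44 participants should be recruited (22 participants per group"), with effect size f = 0.25, "level of significance of 0.05, and power of 95"%. For a within-between interaction with 2 groups and 3 timepoints, and the unstated defaults of correlation 0.5 and no sphericity correction, λ = f²·N·m/(1−ρ) = 0.0625 × 44 × 3 / 0.5 = 16.5 on 2 and 84 df. That gives power 0.956; N = 42 gives 0.946. So 44 reproduces, but it concerns the two PD arms. For PD versus HC there is no calculation, only the statement that "this sample size should be adequate for replicating the previous effects" of an earlier study.

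**Type I error of the t-test at 80 versus 40.** Inputs: n(PD) = 2 × 40 = 80 and n(HC) = 40, from the article; r = PD SD / HC SD, assumed 0.5 to 2; normal data; two-sided 0.05. With the HC SD set to 1:

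- true variance of the mean difference: r²/80 + 1/40
- variance the pooled test uses, on average: [(79r² + 39)/118] × (1/80 + 1/40)

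At r = 2 these are 0.0750 and 0.1128, so the pooled standard error is √(0.1128/0.0750) = 1.23 times too large and the test is conservative. At r = 0.5 they are 0.0281 and 0.0187, so it is 0.81 times the correct size and the test is anti-conservative. Averaging over 200,000 simulated pairs of sample variances gives:

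| PD/HC SD ratio | Pooled t | Welch t |
|---|---|---|
| 0.5 | 0.111 | 0.050 |
| 0.67 | 0.085 | 0.050 |
| 0.8 | 0.069 | 0.050 |
| 1.0 | 0.050 | 0.050 |
| 1.25 | 0.035 | 0.050 |
| 1.5 | 0.026 | 0.050 |
| 2.0 | 0.017 | 0.050 |

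At 60 versus 30, for example after head-motion exclusions, the results are almost the same. At 40 versus 40 the pooled test stays at 0.050 to 0.051. It is the combination of unequal sizes and unequal SDs that matters. A joint regression with HC3 standard errors stays near 5% (checked at an SD ratio of 1.5 either way).

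**Residualising without group.** Suppose the outcome is regressed on a covariate with group left out and the residuals are t-tested. Let d be the group difference on the covariate in within-group SDs. The proportion in PD is 2/3, and 2/3 × 1/3 = 2/9, so the group effect is multiplied by 1/(1 + (2/9)d²). For a true effect of 0.60:

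- d = 0.5 (assumed): 0.60/1.0556 = 0.57
- d = 1 (assumed): 0.60/1.2222 = 0.49

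By simulation with an assumed slope of 0.3 per SD of education, the power lost against a joint model is about 2 points at d = 0.5 and about 7 points at d = 1 (79% to 72%).

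**Dose in a joint model.** Dose is a PD-only variable. Coded as 0 in every control, it carries the group label. With CV the coefficient of variation of dose within PD (assumed), the variance of the PD-HC contrast, in units of the residual variance, becomes 1/80 + 1/40 + 1/(79·CV²) instead of 0.0375.

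| Dose CV in PD | Variance ratio | Power for 0.60 SD |
|---|---|---|
| dose not in model | 1 | 87% |
| 1.0 | 1.3 | 76% |
| 0.8 | 1.5 | 70% |
| 0.5 | 2.4 | 52% |
| 0.4 | 3.1 | 41% |

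The contrast also changes meaning: it compares controls with PD patients extrapolated to zero dose.

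**The case against.** The best defence is that a condensed article may use t-test loosely. The group coefficient in a linear model is tested by a t statistic, so the two sentences could describe a joint model, and the choice between pooled and Welch is commonly left to an analysis plan. This stands in part. A reader might infer that the plan commits to the equal-variance form and so has the wrong error rate because of the 2:1 ratio. The article does not support that: it names no form, and the ratio alone leaves the error at 0.05.

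A reader might also infer that the covariates must be residualised first, so that the PD-HC effect is shrunk as planned. That too goes beyond the text. The regression under Sliding Window Approach acts on the connectivity matrices before clustering, with a different covariate list, and nothing says the temporal measures are treated that way. With an education gap of 0.5 SD the harm would be small in any case.

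The defence also rightly notes that moving every listed covariate into a joint model could do more damage than the wording it replaces, because of dose.

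What the defence does not remove is that the text names a specific test, attaches covariates it cannot hold, and names no model that can. That is a mismatch in what is stated, not a detail left for later.

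**Conclusion.** The concern holds in a limited form. The mismatch between test and covariates is in the text and needs no assumption. The error-rate part is conditional on use of the pooled form and on unequal SDs: about 0.11 to 0.02 over assumed PD/HC SD ratios of 0.5 to 2, a milder 0.069 to 0.035 over 0.8 to 1.25, and no problem at equal SDs. The shrinkage part is conditional on residualising without group and on a group gap in the covariate. The article describes the controls as matched on age and gender but does not mention education, so a gap there is possible; its size is assumed.

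Only the baseline replication check is affected. The randomised Wuqinxi-versus-balance comparison uses a different analysis and is untouched. The change is worth making because this check supports the use of DFC as an outcome and the remedy is nearly free.

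**What to change.** In the PD-versus-HC subsection on group differences in dynamic connectivity:

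1. Replace the t-test on dwell time, fractional windows and number of transitions by one linear model per measure, with group and education fitted jointly and heteroscedasticity-consistent (HC3) standard errors.
2. Use Welch's test where no covariate is used: connectivity strength and the continuous PD-versus-HC rows of Table 1.
3. State that the outcomes of this comparison will not be residualised without group in the model.
4. Leave levodopa and dopamine agonist equivalent dose out of the PD-versus-HC model and examine them within PD only.

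The cost is slightly more analysis work, and marginally wider intervals when the variances are in fact equal. Sample size and data collection do not change.

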## Abstract

**Background:** Parkinson’s disease (PD) is a neurodegenerative movement disease that includes non-motor symptoms such as cognitive impairment. Long-term mind-body exercise has been shown to improve cognitive ability in PD patients, but the methods of assessment and intervention were inconsistent across studies. Wuqinxi is a mind-body exercise that is easy to learn, has few physical and cognitive demands, and is recommended for PD patients. Dynamic functional connectivity (DFC) has been associated with cognitive alterations in PD patients, but no studies have yet explored the effects of Wuqinxi on this association. The current protocol is designed to measure the effects of long-term Wuqinxi intervention on cognition in PD patients, and explore the underlying neural mechanisms through DFC.

**Methods:** A long-term single-blind, randomized trial will be conducted. PD patients and age- and gender-matched HC will be recruited; PD patients will be randomly assigned to either Wuqinxi or balance groups, and HC will all receive health education. The Wuqinxi group will receive a 90-min session of Wuqinxi intervention three times a week for 24 weeks, while the balance group will receive balance exercise instruction on the same schedule. Primary outcomes will include assessment of cognitive domains and dynamic temporal characteristics of functional connectivity. Secondary outcomes will include severity of motor symptoms, mobility, balance, and emotional state. Assessments will be conducted at baseline, at the end of 24 weeks of intervention, and 12 weeks after interventions have ended.

**Discussion:** This study will provide evidence to the effects of Wuqinxi exercise on cognitive improvements in PD patients from the perspective of DFC, and will contribute to the understanding of neural mechanisms underlying cognitive enhancement through Wuqinxi practice.

**Clinical Trial Registration:**www.chictr.org.cn, identifier ChiCTR2000038517.

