### Participants

#### Parkinson’s Disease Patients

##### Inclusion criteria

•Patients with PD diagnosed according to the UK Parkinson’s Disease Society Brain Bank diagnostic criteria.•Age 55–75 years old.•Hoehn and Yahr (H&Y) score of 1–3.•20≤ Montreal Cognitive Assessment (MoCA) score ≤25.•Ability to walk and exercise independently.

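### The test-stage covariates for dwell time, fractional windows and transitions omit age and gender, and the earlier matrix-level regression does not reliably stand in for them; the cognition correlations are most exposed

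*Protocol article*

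**What the plan says.** All places are in the Protocol article.

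- **Sliding Window Approach.** After the Fisher transformation of the windowed matrices, "covariates (age, gender, and education) will be regressed out".
- **Clustering analysis.** The next step is: "A K-means clustering algorithm will be applied to the windowed functional connectivity matrices". Dwell time, fractional windows and number of transitions come from the resulting state assignments.
- **Replication of the previous effects, Group differences in dynamic connectivity.** For PD versus healthy controls (HC), "differences in dwell time, fractional windows, and number of transitions will be examined using two-sample independent" t-tests, followed by "Covariates will include education, levodopa and dopamine agonist equivalent daily doses". The same covariate list is repeated for the Wuqinxi versus balance comparison under Application of DFC in Wuqinxi Intervention.
- **Clinical and Neuropsychological Data Analysis.** Pearson "correlation analyses will be applied between temporal properties and cognition (MoCA and cognitive performance in each domain) in whole PD patients". No covariate is named, here or in the matching section on the intervention.
- **Abstract.** "PD patients and age- and gender-matched HC will be recruited". The eligibility criteria set the same age window for patients and controls ("Age 55–75 years old") and give no further matching rule.
- **Participants' Characteristics.** Levodopa equivalent dose is calculated for PD patients. Table 1 has a dash for it in the PD versus HC column.

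**The concern.** The article treats age and gender as nuisance variables twice, once in preparing the matrices and once in recruiting controls. It then drops both where the temporal measures are tested. Education appears at both stages. No sentence says which stage is meant to adjust the temporal measures.

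The matrix step works on connectivity values, whereas dwell time, fractional windows and transitions describe which state a subject is in and for how long. Subtracting an age-predicted amount from all of a subject's windows need not change how often that subject visits each state. An age effect on occupancy can therefore pass through the regression.

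The within-PD correlations link the two families of primary outcomes and carry the mechanistic argument. If age is related to both state occupancy and cognition, it can produce a correlation that has nothing to do with the disease. Separately, the PD-HC analysis cannot be run as written, because an independent t-test has no place for covariates and one listed covariate exists in only one of the groups.

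**Working it through.** **1. The article's own figure.** No figure depends on the covariate choice. The sample size does reproduce. With f = 0.25, two groups, three timepoints, and an assumed within-subject correlation of 0.5 and sphericity, the noncentrality is f²·N·m/(1 − ρ) = 0.0625 × 44 × 3 / 0.5 = 16.5 on 2 and 84 degrees of freedom. Power is 0.956 at N = 44 and 0.946 at N = 42, so the stated 44 stands and this point does not change it.

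**2. Does the matrix step clear the temporal measures of age?** This was simulated with 120 subjects, two states, 45 edges and 279 windows (304 − 4 = 300 volumes, window 22, assumed step of one volume: 300 − 22 + 1). Age was regressed out of the connectivity values, k-means was re-run, and age was correlated with each measure. All effect sizes are assumed.

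| Age acts on | State separation | Fractional windows, before → after | Dwell time, before → after | Transitions, before → after |
|---|---|---|---|---|
| mean connectivity | poor | 0.74 → −0.01 | 0.32 → 0.00 | 0.51 → 0.02 |
| mean connectivity | moderate | 0.67 → 0.00 | 0.20 → −0.02 | 0.38 → 0.01 |
| mean connectivity | good | 0.64 → −0.02 | 0.44 → −0.02 | 0.23 → 0.01 |
| state occupancy | poor | 0.41 → 0.16 | 0.37 → 0.27 | −0.15 → −0.55 |
| state occupancy | moderate | 0.42 → 0.37 | 0.31 → 0.25 | 0.18 → −0.18 |
| state occupancy | good | 0.38 → 0.38 | 0.24 → 0.24 | 0.25 → 0.24 |

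A separate simulation with 80 subjects and an occupancy effect gave 0.45 before, and 0.42 (subject-level regression) or 0.39 (window-by-window) after. The step therefore removes one kind of age effect completely. It leaves most of the other when states are well or moderately separated. When states overlap, it removes more of the effect on fractional windows but distorts the transition count.

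**3. Within-PD correlations (n = 80).** If the temporal measure and cognition are unrelated given age, the unadjusted correlation is r(age, DFC) × r(age, cognition). The rejection rate of a nominal 5% test follows from Fisher's z: 1 − Φ(1.96 − δ) + Φ(−1.96 − δ), with δ = atanh(r)·√(n − 3) and √77 = 8.775.

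- 0.2 × 0.2 = 0.04: δ = 0.35, rejection 6.4%.
- 0.3 × 0.3 = 0.09: δ = 0.79, rejection 12.4%.
- 0.4 × 0.4 = 0.16: δ = 1.42, rejection 29.4%.

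At n = 44 the range is 5.8% to 17.8%. Table 2 has four rows by seven columns, so 28 such correlations are planned at each timepoint.

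**4. PD versus HC (80 versus 40).** The standard error of the difference in SD units is √(1/80 + 1/40) = 0.194. If age correlates 0.3 with dwell time and an age gap of 0.3 to 0.5 SD remained despite matching, the bias is 0.3 × 0.3 = 0.09 to 0.3 × 0.5 = 0.15 SD. That is 0.46 to 0.77 standard errors, with a type I error of 7.5% to 12%. With no age gap the bias is zero.

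**5. Dose in the PD-HC comparison.** Dose is calculated only for patients. If controls are entered as zero, dose largely tracks group, and the group coefficient describes patients at zero dose, although the article has patients stay on their regular medication.

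**The case against.** *The two lists belong to different steps.* One cleans connectivity values and the other serves the later tests, so they need not match. This stands. A reader might infer a contradiction, but the documents show an unreconciled inconsistency and no more.

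*The regression precedes clustering, so the states are formed on adjusted data.* This also stands. A reader might conclude that the temporal measures are wholly unadjusted for age and gender. The upper half of the table shows otherwise, and the article does not say through which route age acts. The supportable statement is that the step is not reliable for this purpose. The test-stage list also names dopaminergic dose as well as education, so it would be wrong to say that education is the only adjustment.

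*Controls are matched on age and gender.* This disposes of most of the PD-HC bias. A gap of 0.5 SD would give t = 0.5/0.194 = 2.6 and would be visible in Table 1, so the 7.5% to 12% describes matching that has failed. What remains is smaller: no matching rule is given beyond the shared age window, exclusion for head motion can disturb the balance, and an analysis that ignores the matching factors gives a standard error that does not reflect them. With successful matching that last effect normally makes the test conservative, the opposite direction from the inflation under imbalance.

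*The wording of the list is open, and a fuller plan may complete it.* Possibly, but the article does name a list and leaves out the two variables it singles out elsewhere.

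*The correlations are supportive, and MoCA is restricted to 20 to 25 at entry.* Both are fair. The restriction would tend to weaken an age-MoCA correlation, which argues for the lower part of the range.

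**Conclusion.** The point holds in a limited form. No test-stage analysis of dwell time, fractional windows or transitions names age or gender, and the matrix-level regression cannot be counted on to replace them.

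The consequence falls mainly on the within-PD correlations with cognition: a spurious correlation of 0.04 to 0.16 and a rejection rate of 6% to 29% at n = 80. This rests on assumed age correlations of 0.2 to 0.4 with both variables; the article gives no such figures. For PD versus HC the expected bias is small because of the matching.

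A reader might infer that the treatment comparison is compromised. The documents do not support that: the arms are randomised, and a stable age or gender effect cancels within subject in the group-by-time interaction.

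Two defects need no assumed age effect: covariates are attached to a test that cannot carry them, and the PD-HC covariate list includes a variable calculated only for patients. The changes should be made, but the point does not threaten the main randomised result.

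**What to change.** - **PD versus HC temporal measures.** Replace the t-test by a linear model of each measure on group, age, gender and education. Leave dopaminergic dose out of this model and keep it for PD-only analyses such as Wuqinxi versus balance.
- **Correlations with cognition and UPDRS-III**, in both the replication and the intervention sections. Use partial correlations adjusted for age, gender and education at each timepoint.
- **Sliding Window Approach.** Add a sentence that the matrix-level regression does not serve as the adjustment of the temporal measures.

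Age, gender and education are already collected for every participant. With the planned numbers the PD-HC model keeps 120 − 5 = 115 residual degrees of freedom, and a partial correlation in 80 patients keeps 80 − 2 − 3 = 75. The cost is wording and these few degrees of freedom; no new data or participants are needed.
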